### Data Collection System

Data is sent over HTTPS (Hypertext Transfer Protocol Secure) from the patients’ phones to our backend server hosted at our affiliated university. The backend consists of a web application framework with a REST application programming interface. Each request delivered from a patient’s mobile phone app is processed in the backend by extracting request payloads and then transforming the data so that they can be stored in a normalized database. All data were pseudo-anonymized, thus ensuring patient privacy. Patients do not have direct access to their data through the app, although interaction with the clinical team means that they can request their own data. A web-based secure portal has also been created so that anonymized data could be analyzed and hypotheses formed for the future creation of analytics and modeling.

### Patient and Public Involvement

This study was planned with patient and public involvement (PPI) at various stages. Prior to planning the study, PPI meetings were held to gather patient views on remote monitoring. In these sessions, patients were asked to share their views on remote monitoring in general, remote monitoring using wearable and smart devices, as well as familiarity with technology-based solutions. Additionally, the study protocol was submitted to The Urology Foundation (TUF) for peer review as part of the TUF Research Scholarship application. Shortlisting is performed on the basis of PPI and scientific feedback, followed by an interview with a panel consisting of PPI and scientific committee members.

### Availability of Data

The study team will control the final anonymized data set. Requests for access will be reviewed by the trial management group, subject to existing contractual arrangements with the sponsor and funders.

### Ethics and Dissemination

The study has ethical approval from the South West – Cornwall & Plymouth Research Ethics Committee (REC reference 18/SW/0206) and has been registered with the ISRCTN Registry (ISRCTN62293620).

The results of the study will be published in peer-reviewed publications and will be presented at relevant national and international conferences. We will work with our patient panel to develop lay reports to disseminate our research findings to patient groups and the clinical teams at participating sites.

## Results

### Status and Timeline

The DREAMPath study is currently underway at our center. Due to the COVID-19 pandemic, research staff were redeployed to provide clinical cover, but we expect to complete recruitment as planned by the end of the first quarter of 2022.

## Discussion

### Benefits of the Study

The main objective of this study is to measure patient compliance with remote monitoring devices using a multidevice kit for patients in the community setting. This is an important step in order to measure patient engagement prior to any large-scale testing of clinical validity of a remote early warning system in a cohort of patients recovering after major surgery. Similar studies have been reported from prior to the smartphone era [16] and have relied on telemetry to collect data with patients actively reporting data. In the study by Kleinpell et al [16], 725 alarms were generated during a 3-month monitoring period of 10 patients, but only 6 of these alarms led to a clinician consult after phone triage. For remote monitoring to be adopted into routine care, false-negatives need to be kept to a minimum but must still capture all major clinical events. During our data analysis of secondary endpoints, we will explore different early warning systems such as modified versions of the national early warning system [17,18] as well as machine-learning–driven algorithms. Due to the large amount of data being produced, a processing pipeline will be required to ensure that clinical resources are not overburdened by the implementation of remote monitoring.

The current study is designed to be an observational study. Data collected in the study will not be accessible to clinicians until after the completion of the monitoring period, as the study ethics do not allow for clinicians to use this data for clinical decision-making. According to the Medicines and Healthcare Products Regulatory Agency (MHRA) guidelines, any remote monitoring medical apps used that influence clinical decision-making are subject to approval [19]. Similar policies exist in other places including the United States, Australia, and the European Union [20]. If our secondary objective analysis shows that it is feasible to use remote monitoring to pre-empt clinical events, an important next step will be to comply with MHRA and other guidance to ensure that this model is validated for use to facilitate clinical adoption. With a marketplace full of mobile apps that can improve health, regulation is extremely important to ensure that end users are not given false assurances about their health. However, the burden of responsibility must not be passed on to patients to interpret medical data without clinical expertise.

### Strengths and Limitations

This is a proof-of-concept remote monitoring study that aims to measure patient compliance with remote monitoring that could potentially improve postoperative care and reduce hospital readmission. The primary outcome will inform us whether remote monitoring is feasible, and the secondary outcomes will inform us of the clinical usefulness of the data collected.

One limitation is that patients will have access to their own data, which may influence their decision to seek medical attention. Further, as this is a pilot study, the sample size is small. A larger study will be necessary to make conclusions about the overall usefulness of remote monitoring.

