### Study Period

Patients will provide consent either prior to having surgery or in the immediate postoperative period while they are still in hospital. At the time of consent, patients will be familiarized with the smart devices and mobile app described. If the patients undergo cardiopulmonary exercise testing (CPET) as part of their routine assessment, the results for this will be recorded. This data will be used to compare the performance of CPET data and smart device data in predicting postoperative complications.

The 4-week monitoring period will commence upon discharge from hospital. Patients will be expected to wear the wearable device at all times, engage with other devices (see the *Remote Monitoring Equipment* section below for the list of devices) twice a day, and fill out 1 daily questionnaire. Compliance will be defined as completion of 70% of the daily PROM questionnaires or wearing the wrist-worn trackers for at least 10 hours per day over the study duration. A minimum of 1 reading in each hour of either step count or heart rate will constitute a successful hour of data collection. Patients will be given the opportunity to contact dedicated personnel in the study team for troubleshooting purposes only. Furthermore, the app provides clear feedback to patients to signal the successful collection of study data. We hope that this measure will help patients feel supported to engage with the study and reduce patient withdrawal. If patients are admitted to the hospital during the monitoring period, they will not be expected to bring the HALO kit to the hospital, and the admission period and subsequent use will not factor into their compliance rate.

The end of the study will be defined as completion of a 30-day follow-up after discharge from the hospital. Patients will be seen at the clinic or contacted by phone to conclude their participation. Postdischarge events will be collected at this time, which is defined as any unscheduled contact with a health care professional, which includes, but is not limited to, general practitioner (GP) visits, accident and emergency (A&E) visits, home visits by primary care team, etc.

All study assessments are summarized in Table 1, and the study flowchart is illustrated in Figure 1. As DREAMPath is an observational study, patients will be able to participate in other trials.

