### Remote Monitoring Equipment

The HALO kit is designed to be used with a cellular broadband device, such as a 4G-capable mobile phone, which can be used to complete questionnaires electronically. The broadband device remotely uploads data to an anonymized database. Patients will be issued a HALO kit before discharge from hospital and will be monitored remotely for 30 days. The HALO kit consists of 4 devices: a wrist-worn device with step count and heart rate measurement capability, an iHealth Air pulse oximeter, an iHealth Track blood pressure monitor, and a Koogeek Thermometer. These devices are shown in Figure 2. Patients without a smartphone will be provided with one for the duration of the study. Patients will be instructed to wear the tracker continuously and will be shown how to measure blood pressure, pulse oximetry, and temperature twice daily (morning and evening). All readings will be transmitted from the respective device to the iPhone wirelessly, with the option for patients to self-enter data if they prefer to. Additionally, they will be asked to complete a QoR-15 questionnaire once daily.

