**Figure 2 figure2:**
[figure not shown]
Smart devices issued to patients for twice-daily use: bluetooth enabled thermometer, puse oximeter, sphygmomanometer, Apple Watch and iPhone 7 (from left to right).

Patients will be registered and provided with a trial identifier to ensure all transmitted data are anonymized. They will be contacted via telephone to confirm activation of the system. At the time of consent, patients will be informed that the data collected will not be reviewed for clinical decision-making and that the data are anonymized. Unplanned health care engagement such as GP visits, A&E visits, and readmissions will be collected as “events.” Postoperative complications will be recorded per the Clavien-Dindo classification and the postoperative morbidity score. An exploratory study to understand whether there is a relation between the measured physical parameters and health care events will be conducted. If a derangement of physiological parameters can reliably predict an unplanned health care engagement event, a similar remote monitoring solution could be used to triage patients at home instead of the current standard of care in which patients self-present to primary or emergency care facilities. Upon completion of the study, patients will be asked to return the devices, and information about unplanned health care events and adverse events will be collected. Patients will not be held responsible for any lost or damaged devices. Study devices will not have any patient-identifiable data; and in the event of a lost device, they will be remotely wiped using Apple’s remote wipe feature on iOS. Upon return, devices will be cleaned and sterilized in line with hospital ambulatory device policy.

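### Patient access to readings is described inconsistently, and a seen reading may itself prompt the unplanned contact it is explored to predict

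*Protocol article*

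**What the plan says.** On what patients can see, the protocol article says:

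- Discussion, Strengths and Limitations: "One limitation is that patients will have access to their own data, which may influence their decision to seek medical attention".
- Methods, Data Collection System: "Patients do not have direct access to their data through the app". The same sentence adds that "interaction with the clinical team means that they can request their own data".
- Methods, Remote Monitoring Equipment: readings pass wirelessly to the phone, "with the option for patients to self-enter data if they prefer to".
- Methods, Study Period: "the app provides clear feedback to patients to signal the successful collection of study data". This concerns whether data arrived, not their values.

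On the outcome, Study Period says: "Postdischarge events will be collected at this time, which is defined as any unscheduled contact with a health care professional". It gives GP, A&E and home visits as examples, and the text after Figure 2 adds readmissions. Relating these events to the physiological measurements is part of the first secondary objective.

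On the use of the result, the text after Figure 2 opens a conditional sentence, "If a derangement of physiological parameters can reliably predict an unplanned health care engagement event", and concludes that similar monitoring could serve to triage patients at home. Benefits of the Study links a positive secondary analysis to pre-empting clinical events and to the regulatory steps that would follow. The same section says of clinicians: "Data collected in the study will not be accessible to clinicians until after the completion of the monitoring period".

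**The concern.** An analysis of whether readings predict events is easiest to interpret when the readings cannot influence the events. The article closes the route through clinicians during monitoring but states no comparable safeguard for patients, and its own limitation says the patient route is open.

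The event is a contact with care, not a measured deterioration. If a patient sees an abnormal value and telephones the GP because of it, the data show a derangement followed by an event, whether or not the patient was getting worse. An association can then appear with no predictive value behind it, probably most strongly for devices whose values the patient can see. At stake is the secondary analysis that the article says will show how useful the data are clinically. Naming the limitation does not remove the bias, and if the reason for a contact is not asked, no later analysis can recover it.

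**Working it through.** **Step 1: the access statements side by side.** Strengths and Limitations grants access without qualification and names no route. Data Collection System excludes one route (direct, through the app) and allows another (on request). Self-entry requires the patient to have read the value. These can be reconciled if readings show on the device while the app offers no view of stored data, but the article does not say so.

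**Step 2: who starts an event.** GP and A&E visits can be started by the patient, and the text after Figure 2 describes current practice as patients presenting themselves. Readmissions and primary-care home visits may involve a clinician's decision. The article gives no proportions.

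**Step 3: possible size.** The article has no figure to reproduce, so this is an illustration. Let p0 be the background risk of an event over the monitoring period, and q the chance that seeing a deranged reading prompts a contact, independently of p0. Assume no true link between derangement and illness, and no prompting in patients without a seen derangement. Then

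risk after a seen derangement = 1 − (1 − p0)(1 − q), and relative risk (RR) = that risk / p0.

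Both inputs are assumptions. The article's figures of more than 15% within 30 days and more than 20% within 90 days are readmission rates counted from surgery. They are not the risk of any unscheduled contact after discharge, which could be higher, so p0 is varied from 15% to 40%.

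| p0 | q = 5% | q = 10% | q = 20% | q = 30% |
|---|---|---|---|---|
| 15% | 19.25%, RR 1.28 | 23.5%, RR 1.57 | 32%, RR 2.13 | 40.5%, RR 2.70 |
| 20% | 24%, RR 1.20 | 28%, RR 1.40 | 36%, RR 1.80 | 44%, RR 2.20 |
| 40% | 43%, RR 1.075 | 46%, RR 1.15 | 52%, RR 1.30 | 58%, RR 1.45 |

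Example: p0 = 0.20 and q = 0.10 give 1 − 0.80 × 0.90 = 0.28, and 0.28 / 0.20 = 1.40. As odds ratios, the extremes of the table are 1.13 and 3.86.

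**Step 4: what dropping prompted events does.** Suppose every contact in which a reading played a part is recoded as a non-event, including contacts that would have happened anyway. The risk after a seen derangement becomes p0(1 − q), and the RR becomes 1 − q, for example 0.70 at q = 30%. Exclusion therefore errs in the other direction, and neither analysis is unbiased alone.

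**Step 5: information available.** With 30 patients and p0 of 15%, 20% or 40%, the expected number with a background event is 30 × p0 = 4.5, 6 or 12. A restricted analysis would have little to work with.

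**The case against.** The strongest reply is that the article already discloses this risk, calls the analysis exploratory, words the triage sentence conditionally, requires validation before clinical adoption, and says a larger study is needed to judge usefulness. It is also a condensed article, and the event form may sit in the full protocol. Much of this stands. It limits the weight of the point, and the absence of a form is not itself the complaint. What remains is the inconsistent description of access, and a stated use of the association that does not carry the stated limitation through.

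Several stronger readings are tempting and are not supported:

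- *Patients can and cannot see their readings.* No section says they cannot. Data Collection System denies only direct access through the app.
- *The clinician statement is a third contradiction.* It concerns clinicians only. The request route has no stated timing, so a request met after monitoring fits both statements.
- *Incorporation bias.* No reading enters the event definition. The mechanism is a behavioural response that triggers the outcome.
- *Most events are patient-initiated.* The article gives no figure. Only that many can be is supported.
- *Prediction statements should rest solely on events not prompted by a reading.* A patient who is deteriorating, sees a deranged value and seeks help is a true positive. Removing such cases depends on the predictor and pulls the association towards or below the null.

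**Conclusion.** The point holds in limited form. The two descriptions of patient access are inconsistent as written and need to be reconciled. Because the exploratory outcome is any unscheduled contact, a seen derangement may prompt the event it is meant to predict, as the article itself concedes. Under the stated assumptions this alone could produce a relative risk between 1.075 and 2.70. That range shows that the effect can be material. It does not estimate the bias in this study, since neither the background risk nor the prompting probability is given. The primary compliance outcome is not affected. The consequence is for how the physiology-event association may be read, and for what must be recorded while the patient can still be asked.

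**What to change.** 1. Give one consistent description, in Data Collection System and in Strengths and Limitations, of what patients can see on the device, phone and app during monitoring, and when a data request would be met.
2. At the end-of-study contact already planned, record for each event whether a device reading prompted it and whether a reading was shown to a clinician.
3. Report the physiology-event association with all events and, as a sensitivity analysis, without reading-prompted events. State that the restricted version may drop true positives and is biased towards the null.
4. Report readmissions and Clavien-Dindo complications, both already collected, separately as less patient-driven outcomes. Table 1 sets the Clavien-Dindo assessment at one month after surgery while monitoring starts at discharge, so complications should be dated to show which arose after discharge.
5. Word any statement about predicting, pre-empting or triage in the light of all these analyses.

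The cost is one short item per event, one sensitivity analysis and a wording correction. The downsides are that the reason for contact rests on recall, that it may be missing for patients who have already finished (Status and Timeline says the study is under way), and that few events will remain in the restricted analysis.

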### Conclusion

Health care services have undergone a digital revolution during the COVID-19 pandemic. Hospitals were routinely giving patients medical devices to self-monitor, and this initiative was supported by national organizations such as NHS England [21]. This is based on evidence that the prehospital measurements of pulse oximetry can be a red flag for patients who may be experiencing “silent hypoxia” due to COVID-19 infection. However, these devices did not have any way of interacting directly with hospital systems and patients were asked to maintain a diary of readings, which can be reviewed by clinicians via remote consultation or A&E attendances. Our study was conceived prior to the pandemic, but offers an important improvement to the current pathway as patients do not need to enter any data manually as the devices included sync data directly using Bluetooth and our bespoke app allows for an automatic upload. After the completion of this study, we hope to integrate our backend server to communicate directly with hospital electronic health record systems to allow seamless data access for clinicians while patients are at home.

## Abbreviations

A&E: accident and emergency
CPET: cardiopulmonary exercise testing
DREAMPath: Domiciliary Recovery After Medicalization Pathway
GP: general practitioner
HALO: Home and Locally Observed
HTTPS: Hypertext Transfer Protocol Secure
MHRA: Medicines and Healthcare Products Regulatory Agency
PPI: patient and public involvement
PROM: patient-reported outcome measure
QoR: Quality of Recovery
TUF: The Urology Foundation
